### Data collection methods

Pretested structured questionnaires will be used to collect data through face-to-face interviews. Baseline data will be collected at the beginning and the end line data will be collected at the end of the intervention by home-to-home visits of each study participant. Study variables such as socio-demographic characteristics, maternal health service-related variables, male-partners involvement, maternal and paternal knowledge and attitude, and utilization of MWH use will be assessed.

[figure not shown]

**Figure 2:** Sampling Procedure

### Confidentiality

The confidentiality of study participants will be considered. The completed data checklist will be removed from the questionnaires after data collection, and codes will be given to each questionnaire. The removed checklists will be kept in a safe place until it will be discarded. The codes assigned to each participant will be used.

### Data management

Clusters and participant codes will be assigned to each of the completed questionnaires. Data will be entered into Epi info version 7.2.5., edited, and transported to SPSS or STATA software for statistical analysis.

### Description of important terms and measurement

**Maternity waiting home (MWH):** refers to residential lodging, located near a qualified medical facility, where women in their final weeks (2 – 3 weeks) of gestation from geographically isolated areas can wait for their birth and be moved to a nearby health facility shortly before childbirth, or earlier should complications arise. 

**Knowledge and attitude:** Participants knowledge about MWH will be measured using 7 “Yes” or “No” questions. “Yes” will be denoted by “1” and “No” will be represented by “0”. Then the sum average for a respondent above the median will be considered good knowledge and below the median will be considered poor knowledge. In addition, participants’ attitude towards MWH will be measured using 5 points Likert scales (very disagree, disagree, neutral, agree, and very agree). Five questions will be used to measure attitude. Average scores above median will be considered favorable attitude whereas average scores below median will be considered unfavorable attitude.

**Utilization of MWH:** refers to pregnant women's stay at MWH at least for a day.

**Couple:** refers to a married husband and wife who are living together at the time of this study.

**Male partner (MP):** refers to a husband of a woman living with her at time of this study.

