### **Secondary outcomes**

The couples knowledge and attitude will be measured at the baseline and endline (after the follow-up is completed). Consequently, the effect of the intervention on the participants' knowledge and attitudes will be compared between the trial arms.

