### **Statistical analysis**

The data analysis will be performed using STATA or SPSS software. The outcome variables will be computed at baseline and endline for both intervention and control groups. The outcome measures between the intervention and control arms will be compared using the Pearson's chi-square test of independence. The difference-in-difference (diff-in-diff) estimator will be used to estimate the effect of the intervention. Furthermore, we will perform generalized linear model regressions to determine the odds of outcomes between the intervention and control groups. The data will be analyzed using an intention-to-treat approach. The statistical significance will be declared at  $p\text{-value} < 0.05$  with 95% confidence interval.

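### Knowledge and attitude are cut at a median that is not identified and leaves tied scores without a class; the scores themselves would be a better main analysis

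*Protocol*

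**What the plan says.** All references are to the Protocol.

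- **Description of important terms and measurement.** Knowledge is seven yes/no items scored 1 or 0, so the sum takes eight values, 0 to 7. The class rule is that "the sum average for a respondent above the median will be considered good knowledge and below the median will be considered poor knowledge". For attitude, "Five questions will be used to measure attitude", each on a five-point Likert scale, and "Average scores above median will be considered favorable attitude whereas average scores below median will be considered unfavorable attitude".
- **Secondary outcomes.** Both are measured at baseline and endline, and "the effect of the intervention on the participants' knowledge and attitudes will be compared between the trial arms".
- **Statistical analysis.** "The outcome variables will be computed at baseline and endline for both intervention and control groups". Then: "The outcome measures between the intervention and control arms will be compared using the Pearson's chi-square test of independence". A difference-in-differences estimate and generalized linear models giving odds follow, under intention-to-treat.

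A chi-square test and odds need categories, so I read the two-class variables as what is analysed. No section plans an analysis of the scores or gives a fixed cut-off.

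**The concern.** Two of the three specific objectives (male partners' and women's knowledge and attitude) rest on these classes. The rule raises three problems.

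1. **Ties.** 'Above' and 'below' leave a score on the median in neither class, and on an eight-value scale ties are common. Dropping those people would conflict with intention-to-treat. Placing them after the data are seen is a free choice that can move the result.
2. **Unidentified median.** The reported percentages, and in one case the contrast between arms, depend on which median is used.
3. **Lost information.** A two-class version of a score needs more people to detect the same difference.

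**Working it through.** **The plan's own figure.** The Protocol gives no power or sample size for knowledge or attitude. Its figure for the primary outcome does reproduce, and its design effects are borrowed in step 4.
- d_c = 1 + 19 × 0.05 = 1.95; r = 20 × 0.05 × 0.80 / 1.95 = 0.410; d_r = 1 − 0.410² = 0.832.
- Per arm: 2.802² × (0.21 + 0.25) / 0.20² = 90.3; × 1.95 × 0.832 = 146.4; plus 10% = 161.1 (stated 160).
- With n0 = 199: 199 × 1.95 × 0.832 = 322.7, and 322.7 / 20 = 16.1 clusters (stated 320 and 16).

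The Protocol gives no score distribution, so every distribution below is an assumption.

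**Step 1: ties.** With independent items and proportion p correct per item, the tied share is P(X = median) for X ~ Binomial(7, p).

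| p | Median | Share tied |
|---|---|---|
| 0.3 | 2 | 31.8% |
| 0.4 | 3 | 29.0% |
| 0.5 | 4 (see note) | 27.3% |
| 0.6 | 4 | 29.0% |
| 0.7 | 5 | 31.8% |
| 0.8 | 6 | 36.7% |

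Note: at p = 0.5 the median lies on the boundary between 3 and 4; the tied share is the same for either.

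With correlated items (beta-binomial, item correlation 0.1 to 0.4, mean 0.3 to 0.7) the share is 10.7% to 23.7%. Over both models that is 0.107 × 320 = 34 to 0.367 × 320 = 117 women, with men in addition. For attitude, under assumed Likert thresholds, it is about 7% to 10%.

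**Step 2: which median, seven-item score.** Assume 40% correct per item at baseline in both arms, then 50% in control and 70% in intervention at endline. Count ties as not good.
- Baseline: P(X ≤ 2) = 0.420 and P(X ≤ 3) = 0.710, so the median is 3. Good = P(X > 3) = 29.0%.
- Endline pooled: P(X ≤ 3) = (0.500 + 0.126)/2 = 0.313 and P(X ≤ 4) = (0.773 + 0.353)/2 = 0.563, so the median is 4.

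| Cut used at endline | Control good | Intervention good | Difference-in-differences (points) |
|---|---|---|---|
| Endline pooled median (4) | 29.0% → 22.7% | 29.0% → 64.7% | 35.7 − (−6.3) = 42.0 |
| Baseline median kept (3) | 29.0% → 50.0% | 29.0% → 87.4% | 58.4 − 21.0 = 37.4 |

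Control learned, yet its good share falls under the recomputed cut. The contrast between arms stays large and positive under both.

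**Step 3: which median, normal score, effect 0.5 SD.** A recomputed pooled median lies midway between the arms, so control changes by −9.9 points and intervention by +9.9, whatever the gain common to both arms. With the baseline median kept, control changes by Φ(s) − 0.5 and intervention by Φ(s + 0.5) − 0.5, where s is the common gain in SD.

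| Common gain s | DiD, recomputed pooled median | DiD, baseline median kept |
|---|---|---|
| 0 | 19.7 | 19.1 |
| 0.5 | 19.7 | 15.0 |
| 1.0 | 19.7 | 9.2 |

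With no effect both give 0. With medians specific to arm and wave, every share of a continuous score is about 50%, so the difference-in-differences is about 0 by construction. On a discrete score, ties make it erratic around that. A fixed cut is also not neutral: the same 0.5 SD effect reads as 19.1, 15.0 or 9.2 points depending on the common gain.

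**Step 4: information and power.**
- Normal score: relative efficiency of a median split is 4φ(0)² = 2/π = 0.637, a loss of 36.3%.
- Seven-item score with ties put in one class: loss 29% to 54% with independent items (p 0.3 to 0.8), 11% to 43% with correlated items. Dropping ties instead loses about 15% to 25% with independent items.
- Power: effective number per arm = 160 / (1.95 × 0.832) = 98.7. The split compares Φ(d/2) with 1 − Φ(d/2); at d = 0.40 that is 57.9% against 42.1%.

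| Assumed standardised difference d | Power on score | Power on split |
|---|---|---|
| 0.30 | 55.8% | 38.7% |
| 0.40 | 80.2% | 60.6% |
| 0.45 | 88.5% | 70.9% |

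These powers assume complete follow-up of 160 per arm, a normal score, and that the primary outcome's design effects carry over.

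**The case against.** The strongest reply is that the gap is narrow. A reader might infer that the median is recomputed at endline, because outcomes are computed at both waves. The sentence is about the outcome variables and does not mention the median; one baseline median used throughout fits the text equally well. That stands, so the distortion is a possibility and not a stated feature of the plan.

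A reader might also infer that the difference-in-differences would hide or reverse a real gain. The working does not show that for a pooled median. Without a common gain the two estimates are close (19.7 against 19.1 points), and with no effect neither is biased. Only medians specific to arm and wave would erase the contrast, and the Protocol does not specify them.

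Nor can a loss of a third of the information be stated as fact. It is the result for a normal score, and the seven-item range is wide. The Protocol makes no power claim for these outcomes.

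Finally, the choice of median and the tie rule could be in an analysis plan that is not shown. That is fair for those two details. The split itself is fixed in the Protocol, and the case for analysing the scores does not depend on how those details are settled.

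**Conclusion.** The point holds in limited form. From the wording alone, a score on the median has no class and the median is not identified. The size of the consequence rests on assumed distributions: about 11-37% of knowledge scores and about 7-10% of attitude scores tied; an apparent fall in control from 29% to 23% in the worked case if a pooled median is recomputed, against a rise to 50% if the baseline cut is kept; and power of about 61% in place of about 80% at a standardised difference of 0.40. The percentages within each arm are the most exposed. The difference-in-differences is at serious risk only if medians are set by arm and wave. The primary outcome and the sample size are unaffected. This is a cheap improvement to the secondary analyses that should be made.

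**What to change.** In Description of important terms and measurement and in Statistical analysis, make the main analysis of knowledge (0-7) and attitude (5-25 if items are coded 1 to 5) a comparison of the scores between arms. Use the baseline score as covariate, allow for clustering by Kebele, and analyse women and men separately.

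If a good/poor table is kept, set one cut-off before endline data are seen, for example the pooled baseline median for each sex, and state to which class a score on the cut belongs. Use the same cut at both waves and in both arms, and label the table descriptive.

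The cost is wording only: no new items, participants or visits. The downside is that the percentage tables, which are easier for a policy audience to read, become secondary.

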### **Statistical analysis**

The data analysis will be performed using STATA or SPSS software. The outcome variables will be computed at baseline and endline for both intervention and control groups. The outcome measures between the intervention and control arms will be compared using the Pearson's chi-square test of independence. The difference-in-difference (diff-in-diff) estimator will be used to estimate the effect of the intervention. Furthermore, we will perform generalized linear model regressions to determine the odds of outcomes between the intervention and control groups. The data will be analyzed using an intention-to-treat approach. The statistical significance will be declared at  $p\text{-value} < 0.05$  with 95% confidence interval.

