## Protocol summary

**Background:** The majority of maternal deaths occur in low-resource countries such as Ethiopia. Maternity waiting homes (MWHs) can be used as an approach to improve maternal health outcomes by bringing women living in underserved locations to obstetric facilities. However, the use of MWHs in Ethiopia is low. Therefore, it is important to investigate strategies that can effectively improve MWH use in rural Ethiopia.

**Methods:** This study will assess the effectiveness of health education provided to couples on the uptake of MWHs among eligible pregnant women in rural Ethiopia. The couples knowledge and attitude towards MWHs will be assessed as well. Cluster-randomized controlled trials will be the study design. The trial will have intervention and control arms. Randomization occurs at the cluster level. Kebeles are clusters. There will be a total of 16 clusters divided into 8 intervention and 8 control clusters. The outcome assessors will be masked. The trial sample size will be 320 couples (160 in each arm). The intervention will be performed for six months. The content of the intervention will be group health education, take-home print health messages, and individual home visits. Health education will be delivered to the intervention group at baseline, and specific leaflets will be provided. Home visits will be conducted two times (i.e., at 3rd and 5th months of the intervention period). The control group will receive the standard care. Baseline and end line data will be collected. An intention to treat approach will be considered. The Chi-square test will be used to assess the statistical difference between the groups, and the difference-in-differences model will be used to measure the effectiveness of the intervention. Furthermore, generalized linear model regressions will be used to estimate the odds of outcomes between the intervention and control groups. The SPSS and/or STATA software will be used to perform the data analysis.

**Discussion:** The study findings can inform the policymakers and healthcare practitioners to use the intervention modality to improve women's access to maternal health services including MWHs maternity waiting home use among pregnant women with limited access to maternal health services in rural Ethiopia and elsewhere.

**Budget:** The total estimated cost of the study is 222,768 ETB (equivalent to \$4,588 USD).

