## Sample size calculations

The Hooper and Bourke method for cluster randomization studies of parallel arms with repeated cross-sections is used to calculate the sample size. To illustrate within intraclass correlation coefficient (ICC) and between ICC, the technique comprises the measurement of two design effects, with the product of the two being used to inflate the sample size for individual randomization. The within ICC is the correlation between any two pregnant women in the same cluster, while the between ICC is the correlation between any two pregnant women in different clusters. The first design effect ( $d_c$ ) attributable to cluster randomization is measured using a within ICC of 0.05 obtained from a community-based cluster randomized trial in Ethiopia. The design effect ( $d_c$ ) is calculated as:

$$d_c = 1 + (m - 1)\rho$$

Where  $m$  is the cluster size assumed to be 20 (i.e., the total number of pregnant women who will be questioned in each cluster) and  $\rho$  is the within ICC.

The second design effect ( $d_r$ ) attributable to repeated evaluations (baseline/endline) is calculated by using the within ICC and a cluster autocorrelation coefficient ( $\pi$ ) of 0.80.

The second design effect ( $d_r$ ) is calculated as:

$$d_r = (1 - r^2)$$

Where  $r = \left( \frac{m\rho\pi}{d_c} \right)$

The required sample size is then calculated by multiplying the ‘sample size assuming individual randomization’ by both design effects ( $d_c$  &  $d_r$ ). It is calculated as:

$$n = \left[ \frac{(a+b)^2 * (p_1 q_1 + p_2 q_2)}{(p_1 - p_2)^2} \right] * d_c d_r$$

Where:

$n$  represents the sample size in each of the arms i.e., intervention and control

$a$  represents conventional multiplier (1.96) for alpha ( $\alpha = 0.05$ ) and  $b$  represents conventional multiplier (0.842) for power ( $1 - \beta = 0.80$ )

$p_1$  represents proportion of post-intervention users of MWH and  $q_1$  represents proportion of post-intervention non-users of MWH.

$p_2$  represents proportion (50%) of users of MWH taken from a study in Gurage Zone, Southwest Ethiopia  and  $q_2$  represents pre-intervention proportion of non-users of MWH.

$|p_1 - p_2|$  *an effect size* - is an absolute change in proportion of MWH utilization after intervention. It is estimated to be 20%.

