### **Randomization and blinding**

Kebeles' will be the randomization unit whereas the observation or analysis units will be the individual study participants. The selected 16 non-adjacent Kebeles will be listed alphabetically. A restricted randomization with a 1:1 allocation will be used to assign the Kebeles to the intervention or control groups. In Microsoft Excel 2010, a list of random numbers will be created, and the generated values will be fixed by copying them as "values" next to the alphabetic list of the Kebeles. The first eight will be chosen as intervention clusters, and the last eight will be chosen as control clusters, in ascending order based on the produced random numbers. Moreover, a statistician who is blind to the study groups and is not involved in the research will create the allocation sequence and randomize the clusters. The allocation of Kebeles to the intervention or control groups will be hidden from the data collectors or outcome assessors.

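### The stated between-arm test, Pearson's chi-square on individuals, ignores Kebele clustering: at the protocol's own ICC its endline type I error is about 16%, and no clustering adjustment is stated for the difference-in-differences or the regression

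*Protocol*

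**What the plan says.** The Protocol summary fixes the design: "There will be a total of 16 clusters divided into 8 intervention and 8 control clusters". The sample is 320 couples, 160 per arm. Under Sample size calculations, the first design effect "attributable to cluster randomization is measured using a within ICC of 0.05", and m "is the cluster size assumed to be 20". A second factor, d_r, credits the baseline measurement using a cluster autocorrelation of 0.80.

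The Statistical analysis section then compares outcomes between arms by Pearson's "chi-square test of independence. The difference-in-difference (diff-in-diff) estimator will be used to estimate the effect of the intervention". It adds that "we will perform generalized linear model regressions to determine the odds of outcomes", with significance at p < 0.05. The Protocol summary divides the roles: the chi-square assesses whether the groups differ statistically, and the difference-in-differences measures effectiveness. The Primary outcome section also defines effectiveness as a difference-in-differences in the proportion using a maternity waiting home.

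The protocol nowhere mentions a random effect, GEE, a cluster-robust variance, an adjusted chi-square or a cluster-level test. Under Sampling procedure, the same participants are assessed at baseline and endline.

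**The concern.** Pearson's chi-square takes every woman as an independent observation. Here allocation is by Kebele, all intervention couples in a Kebele are invited to one shared education session, and the sample size section itself assumes correlation within Kebeles. The design therefore pays for clustering and the named test then sets it to zero.

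At stake is the p-value for the between-arm comparison of waiting-home use, and of knowledge and attitude if they are tested in the same way. If a significant endline chi-square is read as evidence of effect, a programme with no effect would pass that test far more often than 1 time in 20. The protocol intends its results to guide policymakers.

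**Working it through.** **Inputs, all from the protocol.** 8 Kebeles per arm; m = 20; ICC ρ = 0.05; cluster autocorrelation π = 0.80; two-sided multiplier 1.96; n0 = 199; proportions 50% and 70% (a 20-point effect); 10% loss.

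**1. The protocol's own figure.**
- d_c = 1 + 19 × 0.05 = 1.95
- r = 20 × 0.05 × 0.80 / 1.95 = 0.410
- d_r = 1 − 0.410² = 0.832
- K = 199 × 1.95 × 0.832 / 20 = 16.1

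This agrees with the stated 16 clusters and 320 couples, so the sample size does rest on a design effect of 1.95.

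**2. Endline chi-square.** The true variance of the arm difference is DE = 1 + (m − 1)ρ times the variance that the test assumes. Its real type I error is 2 × [1 − Φ(1.96 / √DE)].

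| m | ICC | DE | Type I error |
|---|---|---|---|
| 20 | 0.05 | 1.95 | 16.0% |
| 18 (after 10% loss) | 0.05 | 1.85 | 15.0% |
| 20 | 0.01 | 1.19 | 7.2% |
| 20 | 0.02 | 1.38 | 9.5% |
| 20 | 0.10 | 2.90 | 25.0% |

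In the first row 1.96 / √1.95 = 1.404, and √1.95 = 1.40 is the factor by which intervals are too narrow. A beta-binomial simulation with 200,000 replicates of 8 against 8 Kebeles (m = 20, ICC 0.05) rejected in 16.1% of null trials at a proportion of 0.5 and 16.3% at 0.3. A t-test on the 16 Kebele proportions with 14 df rejected in 5.0%.

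**3. Difference-in-differences ignoring Kebele.** Let τ be the correlation of one woman's two measurements beyond her Kebele. The protocol gives no value, so τ is an assumption.

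*Four groups treated as independent.* The ratio of true to assumed variance is 1.95 − mρπ − (1 − ρ)τ = 1.15 − 0.95τ.
- τ = 0: 1.15, error 6.8%
- τ = 0.16: about 1.00, error about 5%
- τ = 0.3: 0.865, error 3.5%
- τ = 0.5: 0.675, error 1.7%

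*Individual change scores.* The assumed variance falls to 1 − ρπ − (1 − ρ)τ = 0.96 − 0.95τ in the same units.
- τ = 0: 1.15 / 0.96 = 1.20, error 7.3%
- τ = 0.5: 0.675 / 0.485 = 1.39, error 9.7%; larger τ raises it further

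So the direction depends on τ and on the form of the test.

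**The case against.** **The chi-square is not the measure of effectiveness.** This stands. The Primary outcome section and the Protocol summary give that role to the difference-in-differences. A reader might infer that the trial would declare an ineffective programme effective three times as often as stated, that every p-value is too optimistic, or that no analysis is designated. The documents support none of these. The 16% belongs to the endline chi-square, a difference-in-differences test can err in either direction, and the effect measure is named. What the Statistical analysis section does not say is which p-value decides, and the Protocol summary hands the test of a group difference to the chi-square.

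**The regression may be adjusted in a separate analysis plan.** This stands as well. A generalized linear model can be fitted with GEE or robust errors. Cluster codes go on every questionnaire, and reporting is to follow CONSORT for cluster trials. To say that the regression ignores Kebele would be inference from silence. This does not help the chi-square, which is named outright.

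**The choice of analysis unit is not an error.** In Randomization and blinding, Kebeles "will be the randomization unit whereas the observation or analysis units will be the individual study participants". A reader might take this to mean that individuals are treated as independent. It fits any individual-level mixed model or GEE equally well.

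**The figure depends on the ICC.** True, but the error exceeds 5% for any positive ICC, and 0.05 is the protocol's own value.

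**Conclusion.** The point holds in limited form. The protocol names a between-arm test that is invalid for its design and contradicts its own sample size assumption. The endline chi-square has a type I error of about 16% at ICC 0.05 and 20 per Kebele, about 15% at 18 per Kebele, and 7% to 25% across ICC 0.01 to 0.10. These figures assume equal Kebele sizes. For knowledge and attitude, the same size would also require a similar ICC, which the protocol does not give.

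For the difference-in-differences and the regression, the finding is that no adjustment is stated. If Kebele were ignored, the difference-in-differences test would have about 6.8% error at autocorrelation 0.80 with no individual-level correlation. It would be conservative, or reach about 10%, under other assumptions about τ and the form of the test.

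**What to change.** In the Statistical analysis section and the Protocol summary, drop the chi-square p-value (the proportions can stay as description) and state one primary analysis of the Primary outcome effect that respects the Kebele and uses the baseline. Options:

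- a Kebele-level endline analysis adjusted for the Kebele baseline proportion (13 df), or a t-test on the 16 Kebele-level changes (14 df);
- a mixed model with Kebele, Kebele-by-period and participant effects and small-sample degrees of freedom;
- GEE with a small-sample-corrected robust variance, since 16 clusters are too few for the uncorrected one.

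Apply the same approach to the odds ratios and to knowledge and attitude. A random Kebele intercept alone is not enough: it cancels from a two-period difference-in-differences and implies autocorrelation 1, not 0.80.

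The choice affects power. For 70% against 50%, the standard error is √[(0.21 + 0.25) × V / 160], with power from the noncentral t distribution:

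| Kebele-level analysis | V | Power |
|---|---|---|
| Endline only | 1.95 | about 70% |
| Baseline-adjusted | 1.95 × 0.832 = 1.62 | about 77% |
| Change, τ = 0 | 2 × 1.15 = 2.30 | about 63% |

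Endline only falls to about 68% with 18 per Kebele (V = 1.85, n = 144). Changes beat endline only when 2.30 − 1.90τ < 1.95, that is τ above about 0.18. The baseline-adjusted form matches the d_r factor in the sample size and comes closest to the planned 80%.

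The cost is a wording change and wider, correct intervals. The planned software fits these models, cluster codes are already recorded, and the sentence on analysis units need not change.

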In addition, the following parameters are considered: 95% CI, 80% power, 1:1 allocation ratio of intervention to control, 10% potential loss to follow up, and tabulated sample size ( $n_0 = 199$ ) required to detect a difference in two proportions at 5% significance level with 80% power in literature.  According to Hooper and Bourke, the number of clusters (K) for the sample is determined using the formula  $K = (n_0 d_c d_r) / m$ . The final sample size is calculated by substituting the specified values into the above formula. Hence, a total of 16 clusters are needed, with an approximated final sample size of 320 couples. The two arms each will have 160 couples (pregnant women with their male partners).

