### **Primary outcome**

The proportion of MWH use among participants will be measured. The use of MWH can be traced through individual surveys and MWH record reviews. The proportion of MWH use will be calculated for each trial arm at baseline and end line. The effectiveness of the intervention will be measured as a difference-in-differences in the proportion of MWH use between the trial arms.

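### The effect on MWH use is defined as a difference-in-differences, but significance is given to a chi-square test of another contrast, an odds ratio is added, and no sentence says which p-value decides

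*Protocol*

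**What the plan says.** The Primary outcome section of the protocol defines the effect: "The effectiveness of the intervention will be measured as a difference-in-differences in the proportion of MWH use between the trial arms". The Protocol summary divides the work between two methods: "The Chi-square test will be used to assess the statistical difference between the groups, and the difference-in-differences model will be used to measure the effectiveness".

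The Statistical analysis section keeps that division. First, "The outcome measures between the intervention and control arms will be compared using the Pearson's chi-square test of independence"; the time point is not given. The DiD estimator is then named for estimating the effect. A third method follows: "Furthermore, we will perform generalized linear model regressions to determine the odds of outcomes between the intervention and control groups". The section closes with one threshold, p < 0.05 with a 95% confidence interval, introduced by "The statistical significance will be declared at" and attached to no particular analysis.

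The Sample size calculations section uses a two-sided 5% level ("conventional multiplier (1.96) for alpha") and 80% power for a difference between two proportions.

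**The concern.** An effect measure and the test that supports it should belong to the same contrast. Here the effect is a difference between arms in change from baseline, while the named test of difference is a chi-square between arms. The odds ratio from the generalized linear model (GLM) is a third summary. Read literally, the trial could report a DiD estimate beside a p-value that does not test it.

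Two things are at stake. The first is the error rate: the chi-square as named treats women in the same Kebele as independent, and if more than one analysis may support the claim, the 5% level is not held even with valid tests. The second is the conclusion: when the p-values fall on different sides of 0.05, the protocol does not say which one answers the question.

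This is not a complaint about detail that an unseen statistical analysis plan might supply. The protocol itself lists the three analyses, separates test from estimate and applies one shared threshold.

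**Working it through.** **Inputs from the Sample size calculations section.** Cluster size m = 20; within-cluster ICC ρ = 0.05; cluster autocorrelation π = 0.80; proportions 50% and (by adding 20 points) 70%; multipliers 1.96 and 0.842; tabulated n₀ = 199; 16 clusters, 160 couples per arm.

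**The plan's own figure.**
- d_c = 1 + 19 × 0.05 = 1.95
- r = 20 × 0.05 × 0.80 / 1.95 = 0.410
- d_r = 1 − 0.410² = 0.832
- K = 199 × 1.95 × 0.832 / 20 = 16.1 clusters, or about 323 couples. The stated 16 clusters and 320 couples reproduce.

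**Which analysis the sizing fits.** The factor 1 − r² = 0.83 is the variance factor of an endline comparison adjusted for baseline. A DiD has factor 2(1 − r) = 2 × 0.590 = 1.18. So the sizing fits a third contrast, neither the chi-square nor the DiD.

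**Chi-square as written.** With clustering ignored, the true variance is 1.95 times the assumed one. The effective critical value is 1.96 / √1.95 = 1.404, and the two-sided null rejection rate is 2 × [1 − Φ(1.404)] = 16.0%. A simulation of 16 clusters of 20 gives 16.1–16.2%.

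**Several tests, each valid at 5%.** Assumptions: no true effect, the chi-square replaced by a cluster-valid endline comparison, and any one significant result allowed to count. The endline and DiD statistics correlate at √[(1 − r)/2] = √(0.590/2) = 0.543.

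| Baseline–endline correlation r | Endline or DiD | Adding a baseline-adjusted GLM |
|---|---|---|
| 0 | 8.3% | 8.3% |
| 0.41 | 8.9% | 9.4% |
| 0.8 | 9.5% | 10.2% |
| One valid test decides | 5.0% | 5.0% |

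The range for r is needed because 0.41 comes from a formula for repeated cross-sections, whereas the Sampling procedure section follows the same couples. Cluster-level t-tests on 16 simulated Kebeles, with within-person correlation from 0 to 0.5, give 9.1–9.5% for endline or DiD.

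**Disagreement under the planned effect (50% v 70%, 160 per arm, normal approximation, same variance at both times).**
- Endline: SE = √[(0.21 + 0.25) / 160 × 1.95] = 0.0749; z = 0.20 / 0.0749 = 2.67; power 76%.
- DiD: SE = 0.0749 × √1.18 = 0.0813; z = 2.46; power 69%.
- Both significant, at correlation 0.543: 59.4%.
- Exactly one significant: 76.2 + 69.1 − 2 × 59.4 = 26.5% (endline only 16.8%, DiD only 9.8%). Over r = 0 to 0.8 the figure is 24–34%.

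**The case against.** The strongest reply is that the deciding analysis is already named. The Primary outcome section, the Protocol summary and the Statistical analysis section all attach effectiveness to the DiD. The chi-square can be read as a generic comparison, and the GLM enters as an addition. On that reading the DiD decides and, if it allows for clustering, the error rate is 5%. This largely stands for the effect measure, so it would be too strong to say that the plan leaves the effect undefined. It does not settle the test: no sentence says that the DiD p-value decides, and the summary gives the statistical difference to the chi-square.

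A reader might also infer that the trial's false-positive rate is 9–10% instead of 5%. The documents do not support that as a fact. It needs a rule that any one result suffices, which the protocol does not state; an endline chi-square, though no time point is given; tests that allow for clustering, which the chi-square as written does not; and a GLM that is a distinct third test. A plain endline logistic model would largely repeat the chi-square, and an arm-by-time model would largely repeat the DiD. Either leaves about two effective tests and 8.3–9.5%.

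The 27% is not a rate of contradictory findings. It means only that one p-value is below 0.05 and the other is not. Estimates of opposite sign combined with such disagreement occurred in 0.15% of simulated trials, and none was significant in both directions.

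**Conclusion.** The point holds as a mismatch between effect measure and test, with the deciding p-value left open. The firmest figure is the chi-square's own null rejection of about 16%, which follows from the protocol's ICC of 0.05 and cluster size of 20. The 8–10% is conditional: it applies if more than one analysis may count and each is valid for clustering, with r between 0 and 0.8. The 27% rests on the planned 50% v 70%, r = 0.41 and a normal approximation. The matter should be corrected because, as written, a DiD effect can be declared significant on the p-value of a different contrast that ignores clustering.

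**What to change.** In the Protocol summary, Primary outcome and Statistical analysis sections, state that the intervention effect on MWH use from one cluster-accounting model, two-sided at 0.05, is the only deciding test. The smallest change is to use the DiD already named, tested by its arm-by-time term. If the sponsor prefers to match the 1 − r² factor behind the sample size, the baseline-adjusted endline effect can take that place, and the Primary outcome section should then say so.

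Report the chi-square and the remaining analyses of MWH use as supportive, with estimates and 95% confidence intervals, and state that they cannot by themselves support a claim of effectiveness.

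The cost is a few sentences in three sections, with no new data or participants. The downside is that a favourable p-value from a supportive analysis can no longer be claimed as the trial's result.
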